## Abstract

**Background:**

Loss of masticatory function consequent to tooth loss has been associated with changes in food choices and insufficient nutritional intake. To date, interventions based on dental prostheses alone did not significantly improve nutrient intake. Pilot studies have shown positive impacts of interventions combining implant-supported fixed dental prosthesis with brief dietary advice. The relative contribution and the potential synergy of the components of such interventions need to be determined as it has major public health implications for the community-dwelling aging population that continues to disproportionately suffer from tooth loss and its consequences.

**Objective:**

To assess the effect of rehabilitation of masticatory function with fixed implant supported dentures and nutrition education in older subjects with terminal dentition (stage IV periodontitis) or full edentulism.

**Methods:**

A 2 × 2 factorial randomized controlled trial with 16-month follow-up of eligible adults (≥60 years) with loss of masticatory function consequent to full arch edentulism or terminal dentition (*n* = 120) will be conducted to test whether the rehabilitation of masticatory function with fixed implant supported dentures, nutrition education and/or their combination improves intake of fresh fruits and vegetables for aging subjects. The study has been designed to detect changes in fresh fruits and fresh vegetables intake at 4 months using the 24-h dietary recall method. Changes in protein as percentage of total energy, nutritional biomarkers, plasma metabolomics, oral and gut microbiome, quality of life and masticatory function will also be assessed.

**Discussion:**

We hypothesize that receiving rehabilitation of masticatory function with fixed implant dentures together with nutrition education is the most effective intervention for improving nutrient intake in aging community-dwelling subjects with extensive tooth loss. The results of this study will assist in designing better treatment regimens, guide medical care for individual subjects, and inform public health and policy.

**Clinical Trials Registration:**

NCT05334407.

## Introduction

Over the course of life unmanaged caries and periodontitis, the most common diseases of mankind, lead to tooth loss and associated loss of quality of life and eventually compromised masticatory function. Older adults and aging subjects may be disproportionately affected (1). At the end of the disease spectrum, subjects with complete tooth loss (edentulism) or presence of only few remaining teeth that do not enable adequate chewing function show changes in their food choices and seem to prefer softer diets with higher carbohydrates and fat and less fresh fruits and vegetables (2, 3).

Accumulating evidence points to the presence of an association between changes in dietary behavior consequent to tooth loss and insufficient nutrition intake (4–6). A recent systematic review indicated that subjects lacking a functional dentition had a 21% increased likelihood of being at risk of malnutrition or being malnourished (7). Such impaired nutrition may have long term effects on muscle strength and physical decline and be detrimental to general health (8, 9). Indeed, the recent Global Burden of Disease study of dietary risk factors identifies 15 important disease associated exposures. Their analysis shows that 5 of the health associated exposures: consumption of fruit, vegetables, whole grains, nuts, and fiber require a good level of mastication (10).

A recent systematic review has addressed the efficacy of tooth replacement with dental prostheses and identified clear benefits in terms of restoration of masticatory function (11). Among fully edentulous subjects, greater benefits have been observed with dental implant retained prostheses with respect to conventional dentures.

While the physiology of mastication is an essential component of alimentation and contributes to the broader process of nutrition, recent research has focused on the nutritional benefits of tooth replacement to better focus the relevance of oral health on general health. Several studies have tried to improve the nutrient intake among edentulous individuals with various types of dentures. However, this goal has been elusive for interventions based on either complete dentures or implant-retained overdentures, given the functional limitation on these prostheses and perhaps the lack of concomitant dietary intervention (12–15). A small-scale case series has shown that implant-supported fixed prosthesis resulted in more efficient mastication and improved nutrient intake compared with conventional and implant-based removable dentures in partial edentulism (16).

Within dentistry, the long-held assumption that restoration of masticatory function alone—i.e., without dietary re-education intervention—brings nutritional benefits is being questioned. Sparse evidence points to the positive impact of nutrition counseling on the dietary intake of edentulous subjects receiving dental prostheses: brief dietary advice has been advocated to help patients take full advantage of the enhanced masticatory function to improve their diet (17, 18). Ellis et al. further showed that the impact of dietary advice on patient's satisfaction with dentures and oral health-related quality of life depends on the nature of the prosthesis (19). A recent systematic review on the impact of oral rehabilitation coupled with dietary advice on nutritional status has indicated that in most studies the dietary interventions were not theory based and poorly described (20). Not unexpectedly, the meta-analysis found only a trend toward significant changes in fruit and vegetable consumption and marked heterogeneity among the included pilot case series. No trial has been performed to assess the benefit of dietary advice alone or the combined effect of re-establishment of masticatory function with an implant-supported fixed prosthesis and dietary advice in edentulous elderly subjects. Understanding the relative contribution of restoration of masticatory function and nutrition education is critical to design effective interventions and improve public policy related to nutrition and prevention of physical decline in aging populations.

Based on the current equipoise about the relative contribution of dental and dietary interventions and the clinical and public health relevance of defining appropriate interventions to improve nutrition of older adults with extensive tooth loss, this protocol describes a 2 × 2 factorial clinical trial to assess the effect of rehabilitation of masticatory function with fixed implant supported dentures and/or brief nutrition education on the dietary intake and nutrition in older subjects with terminal dentition (stage IV periodontitis) or full edentulism. The clinical trial is being implemented. The effectiveness of the intervention will be validated during the trial. Results will identify the relative importance and optimal sequence of dental and dietary interventions, providing critical information with major implications for caring of individual subjects and for public health and policy. The results of the clinical trial will be available in 2 years.

## Methods and Materials

### Study Design

This protocol has been prepared according to the SPIRIT guideline for clinical trial protocols (21).

#### Study Overview

The study is designed as a factorial randomized controlled clinical trial testing the benefits of dental and/or dietary interventions on changes in fresh fruits and fresh vegetables intake at 4 months (Table 1). Group A (DE+/DI+) will receive the full treatment regimen. Group B (DE+/DI–) will receive implant-supported fixed prosthesis at first and nutrition education after a 4-month waiting period. Group C (DE–/DI+) will receive the nutrition education at first and implant treatment after a 4-month waiting period. Group D (DE–/DI–) will receive the same treatment as Group A after a 4-month waiting period (Figure 1). The waiting period is equal to the current waiting list in the department. Subjects will be followed for an additional 12-month period. All procedures will follow the principles of the Declaration of Helsinki on experimentation involving human subjects, all subjects will provide written informed consent. The trial has been approved by the Institutional Review Board of the Shanghai Ninth People's Hospital, Shanghai Jiao Tong University School of Medicine (Approval No. SH9H-2021-T321-3) and is registered in ClinicalTrials.gov (NCT05334407). The trial will be independently monitored by the office of clinical research of the Shanghai Ninth People's Hospital. Any modifications to the protocol with impact on the conduct of the study will require a formal amendment to the protocol. The SPIRIT summary of the trial procedures is illustrated in Supplementary Table 1.

**Table 1 T1:** Overview of the schedule of enrolment, interventions, and assessments.

	**Study period**							
	**Enrolment**	**Allocation**	**Post-allocation**					**Close-out**
**Timepoint**	**−7 ±7 d**	**0**	**−0 ±7 d**	**4 m ±14 d**	**8 m ±14 d**	**12 m ±14 d**	**16 m ±14 d**	
Intervention^*^			**DE**	**DI**	**DE**	**DI**		
**Enrolment**								
Eligibility screen	X							
Informed consent	X							
Demographics	X							
Medical history	X							
Concomitant medications	X							
Allocation		X						
**Interventions**								
[Group A:DE+/DI+]			X	X				
[Group B:DE+/DI–]			X			X		
[Group C:DE–/DI+]				X	X			
[Group D:DE–/DI–]					X	X		
**Assessments**								
*24-h dietary recall*	X			X				
*food-frequency questionnaire*	X			X	X	X	X	
*Anthropometric measurement*	X			X	X	X	X	
*Masticatory function*	X			X	X	X	X	
*Peri-implant soft tissue condition*				X	X	X	X	
*OHIP-14*	X			X	X	X	X	
*Blood sample*	X			X	X	X	X	
*Saliva sample*	X			X	X	X	X	
*Subgingival plaque sample*	X			X	X	X	X	
*Stool sample*	X			X				
*Nutritional status*	X			X	X	X	X	
*Muscle strength*	X			X	X	X	X	
*Cognitive function*	X			X	X	X	X	
*Depressive symptoms*	X			X	X	X	X	

* *Interventions included DE (dental intervention) and DI (Dietary Intervention)*.

**Figure 1 F1:**
[figure not shown]
Study flow chart.

#### Recruitment

Older subjects (≥60 years of age) with full arch edentulism or terminal dentition seeking care at the Dept. of Oral and Maxillofacial Implantology of Shanghai Ninth People's Hospital will be screened and invited to participate while attending new patient clinics.

#### Eligibility Criteria

All potential participants will be assessed for eligibility based on the inclusion and exclusion criteria.

##### Inclusion Criteria

Being edentulous or having a terminal dentition (22) and accepted treatment plan for fixed implant-supported prosthesis restoring at least 10 pairs of occluding teeth.Self-reported inadequate fresh vegetables or fresh fruits or protein foods intakes (daily intake thresholds based on the Chinese Dietary Guidelines for the Elderly recommendations).Understanding written and spoken Chinese and ability to respond to Chinese questionnaires.Able and willing to give informed consent for participation in the study.Able and willing to comply with 12-month follow-up.

##### Exclusion Criteria

General and local contraindications to implant-supported immediate-loading fixed prosthesis.Looking for replacement of existing implant-retained overdenture with implant-supported fixed denture treatment.Presence of infectious disease, acute or chronic symptoms of TMJ disorder.Psychiatric disorder, dementia.Any dietary restriction, currently taking nutrient supplements or inability to choose his/her diet.Uncontrolled diabetes (HbA1c ≥ 7.0%).Self-reported heavy smokers (>10 cigarette/day).

#### Screening

Screening evaluations for this study will be performed in the context of routine patient evaluation in the clinic. The investigators will approach consecutive patients with the condition for possible inclusion in the study. During screening the investigator will also verify eligibility criteria. Additionally, social media (WeChat & Weibo) advertisement will be utilized to help recruit study participants. For some of these subjects, initial screening will be performed by phone. Following the telephone screening, the potential subjects will be invited for clinical screening evaluation.

#### Enrollment

Subjects fulfilling the inclusion and exclusion criteria will be invited to participate in the study and receive an explanation of the study, its objectives, benefits and risks by the investigator in the context of informed consent. The following information will be collected and recorded after the inclusion of the participants.

(1) Demographics: date of birth, gender, education, ethnicity, family income and anthropometric measures.(2) Lifestyle factors: smoking (including tobacco consumption and smoking history), drinking habits and oral hygiene habits using the items from the Fourth National Oral Health Survey Questionnaire in Mainland of China (23) will be recorded.(3) Health literacy: oral health literacy will be recorded using the Chinese version of the Short-Form Health Literacy in Dentistry (HeLD) scale (24) and nutrition literacy using the Nutrition Literacy Questionnaire for the Chinese Elderly (25).(4) Medical History: Details of medical, including diabetes mellitus, cardiovascular diseases and other systemic diseases will be recorded. For subjects with diabetes, levels of glycated hemoglobin (HbA1c) will be obtained from the patients' medical records.(5) Concomitant Medications: All over the counter or prescription medication, vitamins, and/or herbal supplements will be recorded on CRFs.

#### Randomization

Subjects will be randomly assigned to one of four groups with a 1:1:1:1 ratio by stratified block randomization. The block size will be 8 and stratifying factors will be diabetes status and smoking. Subjects will be registered into the study by a study registrar who will assign the treatment number and organize the sequence of the bookings of the patient according to the random allocation. The registrar will not be involved in any other study procedures.

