#### Blinding and Allocation Concealment

Timing of treatment will be concealed to the therapists and to the examiners. Two separate masked therapists will perform the dental or the nutritional interventions. All laboratory assessments will be performed blindly.

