### Study Intervention

#### Treatment of Trial Participants

The treatment process will include provision of implant-supported full-arch fixed prostheses (dental intervention, DE) and dietary intervention tailored to the dental status (dietary intervention consisting of nutrition education, DI). Subjects will be randomized to either a waiting period or treatment regarding dental intervention and dietary intervention. Ethical justification for the waiting period comes from the current waiting list in the regular care at the hospital. In order to improve the compliance with the protocol, all subjects participating in the study will have an alert in their patient record identifying them as participants to this protocol to alert administrative staff on the need to follow a stringent timing of follow-up appointments.

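### One fixed, published block size of 8 leaves an avoidable risk that a recruiter who follows past allocations can foresee some dental timings

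*Protocol article*

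**What the plan says.** The Randomization section of the protocol article states: "Subjects will be randomly assigned to one of four groups with a 1:1:1:1 ratio by stratified block randomization". It continues: "The block size will be 8 and stratifying factors will be diabetes status and smoking". With four arms, a block of 8 contains two patients per arm. Groups A and B receive dental treatment early. Groups C and D wait; of Group C, for example, the Study Overview says "Group C (DE–/DI+) will receive the nutrition education at first and implant treatment after a 4-month waiting period". Seen as early against delayed dental treatment, each block is therefore four and four.

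Two safeguards are stated. The Randomization section gives allocation and booking to a separate person: "Subjects will be registered into the study by a study registrar who will assign the treatment number and organize the sequence of the bookings", and "The registrar will not be involved in any other study procedures". The section on blinding and allocation concealment adds: "Timing of treatment will be concealed to the therapists and to the examiners".

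Recruitment is described under Screening: "The investigators will approach consecutive patients with the condition for possible inclusion in the study". The investigators also verify eligibility and, under Enrollment, explain the study as part of consent. No section says whether they can see past allocations, and none says that they are kept from them.

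**The concern.** An independent registrar stops anyone looking up the next allocation. That does not stop someone inferring it. With one known block size, past allocations alone show when one timing has been used up within a block, and the rest of that block is then certain. The size is in a public article.

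Past dental timing is visible in practice. The schedule table places dental treatment for Groups A and B within about a week of allocation, and that treatment is implant surgery with an interim fixed prosthesis. Groups C and D wait. All of this happens in one department. Diabetes and smoking status, which define the strata, are known to whoever enrols the patient.

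There is some room to act on a forecast. Eligibility includes self-reported inadequate intake, contraindications to implants and an accepted treatment plan, so a patient could be hurried in or held back. If that happened, the arms could differ at entry in ways that affect diet, in a trial of 120 patients whose primary outcome comes from recall interviews.

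**Working it through.** The protocol gives no predictability figure, so there is none to reproduce. The check asks how many allocations are certain to an observer who knows the block size and every earlier allocation in the stratum.

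**Inputs.**
- Randomization section: four arms at 1:1:1:1, block size 8, two stratifying factors.
- Study Overview: two arms early and two delayed for dental treatment, so m = 4 of each per block.
- Sample Size section: 30 per group, 120 in total.
- Assumption: each stratifying factor has two levels, giving four strata.

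**Dental timing, filled block.** There are C(8,4) = 70 equally likely early/delayed orderings. An allocation is certain once one of the two timings is used up.

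| Position in block | 1–4 | 5 | 6 | 7 | 8 |
|---|---|---|---|---|---|
| Probability that it is certain | 0 | 2/70 = 0.029 | 10/70 = 0.143 | 30/70 = 0.429 | 1 |

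The sum is 1.6 per block, which agrees with 2m/(m+1) = 8/5. The share is 1.6/8 = 20.0%. Single blocks vary: 1, 2, 3 or 4 certain allocations occur with probability 57.1%, 28.6%, 11.4% and 2.9%, so one block can reach 4/8 = 50%.

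**Unfilled last blocks.** Certainty arises late in a block, so incomplete blocks lower the share.
- Four strata of 30: each has three full blocks and six further positions, (3 × 1.6 + 0.171)/30 = 16.6%.
- Strata drawn at random with assumed diabetes and smoking shares between 15% and 30%: about 18% on average, with 95% of simulated trials between about 17% and 19%.
- All blocks filled: 20%.

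Over 120 patients, 16.6% to 20% is about 20 to 24 patients.

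**Exact arm.** The last allocation of a filled block is always certain. The seventh is also certain when the last two belong to the same arm, which has probability 1/7. The expected number is 1 + 1/7 = 1.14, and 1.14/8 = 14.3%.

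**Best guess at each allocation, filled blocks.** The guess is right for 5.33/8 = 67% of dental timings (50% by chance) and 3.76/8 = 47% of exact arms (25% by chance).

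**Varying block sizes.** Simulation, with an observer who sees every past allocation and knows the set of sizes but not their order:
- Sizes 8 and 12: certain dental timings are 4% in one simulation and 6% in another.
- Sizes 4, 8 and 12: 3% and 5%.
- The best-guess rate for timing with sizes 8 and 12 is about 64%. Adding blocks of 4 should not improve on that, because a fixed block of 4 is itself more guessable (70.8%).

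**The case against.** The strongest reply is that these figures describe an ideal observer. The recruiter must know the size, follow every earlier timing separately in each stratum, know where blocks begin, and learn each allocation before the next patient of that stratum enrols. No section says that recruiters see past allocations, and giving bookings to the registrar limits routine exposure. This stands: the figures are a worst case, and the likely level is unknown.

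A reader might infer that the trial cannot be masked at all. The documents do not support that. They state that timing is concealed from therapists and examiners. Whether that concealment would work is a separate question. Here it matters only that recruiting investigators are not named in it.

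A reader might also take the record alert as a leak, since participants "will have an alert in their patient record identifying them as participants to this protocol". The alert marks participation in all four arms and is meant to keep appointments on time. Nothing says that it shows the group, so it adds no support.

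Other features reduce motive and opportunity. Patients are to be approached consecutively, an accepted treatment plan is required at entry, every arm eventually receives both interventions, and the wait equals the department's existing waiting list. These lessen the risk without removing it, because eligibility still includes judgement and self-report.

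Finally, a block of twice the number of arms with an independent registrar is a workable choice, and varying the size hardly changes the average guess rate. Both points stand. The gain is in removing certainty.

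**Conclusion.** The point holds as a minor, avoidable weakness in a stated design choice. The section contains no error or contradiction. A fixed, published size of 8, visible treatment timing and no stated concealment from those who screen and consent would let a fully informed recruiter be certain of about 17–20% of dental timings and up to about 14% of exact arms.

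This rests on complete tracking by stratum, on four strata, and for the lower end on unfilled last blocks. The 20% is an average over filled blocks, not a ceiling for any one block.

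Two stronger readings are tempting. One is that a fifth of allocations are in fact predictable to the recruiting team; the documents do not establish that recruiters have the knowledge this needs. The other is that the trial's results will be biased; predictability percentages are not estimates of bias in fruit and vegetable intake, and nothing in the documents allows such an estimate.

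**What to change.** By amendment, for blocks not yet started in each stratum, use randomly permuted blocks of varying size, for example 8 and 12, or 4, 8 and 12. Blocks already open run to their end. Withhold the sizes from everyone who screens, consents, treats or assesses patients. In the Randomization section, replace the statement of block size with *randomly permuted blocks of varying, undisclosed size*, and keep the two stratifying factors.

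For the same fully informed observer, certain dental timings fall from about 17–20% to roughly 3–6%. The average guess rate falls only from about 67% to 64% (sizes 8 and 12), so the change should be presented as removing certainty.

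The costs are small but real. The Introduction says that the trial is being implemented, and the Study Overview requires a formal amendment for changes that affect conduct. The unused part of the list must be regenerated. An unfilled block of 12 can leave two arms in a stratum up to 12/4 = 3 patients apart, against 8/4 = 2 with a block of 8. Arms, sample size, stratification and patient care do not change.

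### Dental status (edentulous v terminal dentition) enters neither the stratification nor the stated ANOVA: a modest loss of precision that one pre-specified model term would recover

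*Protocol article*

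**What the plan says.** All references are to the protocol article.

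- **Inclusion Criteria** admit two kinds of patient: "Being edentulous or having a terminal dentition (22) and accepted treatment plan for fixed implant-supported prosthesis". The expected mix is not given.
- **Randomization**: "Subjects will be randomly assigned to one of four groups with a 1:1:1:1 ratio by stratified block randomization", and then "The block size will be 8 and stratifying factors will be diabetes status and smoking". Dental status is not a factor.
- **Exclusion Criteria** narrow both stratification factors: "Uncontrolled diabetes (HbA1c ≥ 7.0"%) and "Self-reported heavy smokers (>10 cigarette/day") are excluded. Patients with better-controlled diabetes and lighter smokers can still enter.
- **Statistical Analysis Plan** tests dental treatment, dietary advice, their combination and their sequence by ANOVA, with Kruskal–Wallis for non-normal data. It names no baseline covariate and no stratification factor.
- **Discussion** explains why the severe end of tooth loss was chosen: such patients are expected to have larger dietary changes and to gain more masticatory function from tooth replacement.
- **Dental Intervention** has remaining teeth extracted at the implant surgery. **Oral and Fecal Microbiome** has a separate sampling step for dentate patients, so dental status is known at baseline.

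**The concern.** A stratification factor, or a covariate, earns its place by predicting the primary outcome, here the 4-month change in fruit and vegetable intake. The protocol's own reasoning makes dental status a plausible predictor. The comparison condition also differs by dental status. While they wait, terminal-dentition patients in the delayed-dental groups still have their remaining teeth, and edentulous patients have none. The planning mean and SD come from edentulous older people only, so no planning figure covers the other group.

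If dental status does predict the outcome, leaving it out of both the allocation and the analysis puts its variance into the error term. Standard errors are then wider than they need to be. The trial sits close to its 80% power target, so a cheap gain in precision is worth having.

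**Working it through.** **Inputs from the Sample Size section**
- Intake 255 g/day with SD 200 g. This is the SD of intake level; no SD of change is given, so 200 g is used for the outcome.
- Assumed increases: 50 g (dental alone), 70 g (advice alone), 245 g (both). A control change of 0 g is assumed here.
- Alpha 0.05 (taken as two-sided), power 80%, 20% loss, 30 per group. Evaluable: 30 × 0.8 = 24 per group, or 48 v 48 for a factorial margin.

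**Inputs not in the documents, assumed**
- Edentulous share p = 0.5.
- Outcome difference D between edentulous and terminal-dentition patients: 50, 100 or 150 g.

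**Step 1: reproduce the plan's sample size.**
Dental main effect = [(50 − 0) + (245 − 70)]/2 = (50 + 175)/2 = 112.5 g.
n per margin = 2 × [200 × (1.960 + 0.842)/112.5]² ≈ 49.6, so 50, or 25 per cell. Allowing for loss, 25 × 1.2 = 30 or 25/0.8 = 31.25, so 32. The planned 30 is reproduced to within two patients.
Power at 48 v 48: SE = 200 × √(2/48) = 40.8 g; 112.5/40.8 − 1.96 ≈ 0.80, giving 78.7%.

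**Step 2: gain from accounting for dental status.**
Residual SD = √(200² − D² × p(1 − p)) = √(40,000 − D²/4).

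| D (assumed) | Residual SD | Power, 112.5 g main effect (48 v 48) | Power, 50 g dental-alone contrast (24 v 24) |
|---|---|---|---|
| not accounted for | 200 g | 78.7% | 13.7% |
| 50 g | 198 g | 79.3% | 13.8% |
| 100 g | 194 g | 81.2% | 14.3% |
| 150 g | 185 g | 84.4% | 15.3% |

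**Step 3: how far chance imbalance could move an estimate.**
95% limit of the difference in edentulous share = 1.96 × √(2p(1 − p)/n). Shift = limit × D.

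- Main effect, 48 v 48: limit 20.0 points; shift 10, 20 or 30 g for D = 50, 100 or 150 g. For scale, 1.96 × SE from all sources is 80 g.
- Dental alone, 24 v 24: limit 28.3 points; shift 14, 28 or 42 g. For scale, 1.96 × SE is 113 g.
- To equal 112.5 g, D would have to be 112.5/0.200 ≈ 562 g. With a total SD of 200 g and p = 0.5, D cannot exceed 200/√0.25 = 400 g.
- To equal 50 g, D would have to be 50/0.283 ≈ 177 g, with the imbalance at its 95% limit.

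**The case against.** The case on the other side is substantial.

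- **The premise is not quantified.** The documents give no edentulous share and no difference in intake or response between the two groups. The Introduction treats complete tooth loss and a few non-functional teeth as one end of a spectrum, and the Discussion contrasts severe with milder tooth loss, not edentulous with terminal dentition. Every participant must also report an inadequate intake. This stands: the gain in Step 2 depends on D, and at 50 g it is negligible.
- **Chance imbalance is not bias.** A reader might infer that an imbalance in dental status could imitate or mask the dental effect. Step 3 does not support that. Within the assumed range the shift never reaches even the 50 g dental-alone effect, and it cannot reach the 112.5 g main effect if the SD is 200 g. Under randomisation this variation is already in the standard error and the type I error rate. The dental-alone contrast is weak whatever the dental balance, which is a separate matter.
- **The chosen strata are defensible.** A reader might infer that the exclusions make diabetes and smoking useless as factors. They narrow the range, but both still vary, and the trial also measures peri-implant, inflammatory and microbiome outcomes. The documents do not show that smoking should give way to dental status.
- **The diet exclusion.** A reader might also infer that "Any dietary restriction, currently taking nutrient supplements or inability to choose his/her diet" empties the diabetes stratum. Nothing shows how many patients with diabetes it would remove, so that is speculation and no ground for rewriting the criterion.
- **Covariates are often left to a separate analysis plan.** True, and if such a plan already contains this term the point is closed. The article does, however, state the strata and the form of the analysis, and dental status is in neither.

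**Conclusion.** The point holds as a modest matter of precision. A plausible prognostic factor, known at baseline and closest to the dental question, is left out of both the allocation and the stated analysis. Accounting for it would add about 0.6, 2.5 or 5.7 percentage points of power for the dental main effect (79.3, 81.2 or 84.4 minus 78.7) at assumed differences of 50, 100 or 150 g.

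These figures rest on an assumed 50% edentulous share, on 200 g as the SD of the outcome, on no change in the control group and on 20% loss. A more uneven mix would shrink the gain. The validity of the randomised comparison is not in question.

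**What to change.** Keep the current randomisation; the article says the trial is already being implemented. Before outcome data are examined by group, pre-specify that the primary 4-month model contains the dental and dietary factors and their interaction, baseline dental status (edentulous v terminal dentition), and the two stratification factors already used. Define dental status per patient, including how to class someone whose two jaws differ, since the dental intervention may involve only one jaw.

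The cost is one model term for dental status, plus one each for diabetes and smoking if these are binary. With 96 evaluable patients and four cells, residual degrees of freedom fall from 92 to 89. One limit should be noted: the Kruskal–Wallis fallback takes no covariates, so the gain is realised only if the model remains the primary analysis.
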